### Design and Organization of a Physical Activity–Promoting Intervention

All participants will participate in the target group-specific community-based PA intervention. The pilot study’s intervention period is 12 months per participating neighborhood. The participants will be encouraged to continue to engage in PA independently (Figure 2).

The intervention’s main component will comprise regular PA meetings organized in so-called “activity tandems,” which take place once a week for 30-45 minutes. One activity tandem will include 1 trained voluntary mentor and 3-4 older adults living in the same neighborhood. These activity tandems will primarily engage in low-threshold outdoor PA and exercise together in their neighborhood. For this, easily accessible locations such as urban lawns, walking paths, parks, and fitness trails will be used. In case of bad weather, the PA meetings will be organized in the meeting places of collaborating partners, for example, community centers. Due to the small group size, the content of each tandem lesson can be flexible and tailored to the individual participant’s needs. For example, the exercises can be performed at different levels of intensity, or alternative exercises can be selected from a large PA-exercise pool. Additionally, monthly group meetings (eg, 3-4 activity tandems with a total of 12-16 older adults) will be organized in each neighborhood district in the intervention months 5-12 (Figure 2), which will be delivered by trained exercise instructors. In these group meetings, in addition to PA exercises, the following contents will be covered: knowledge about the positive effects of PA, goal setting and planning, barrier management, and motivational aspects, as well as the sustainable implementation of regular PA in everyday life. Measures like small group sizes, qualified mentors, support material (eg, first aid kits, pulse oximeters, Borg scales), and the accessible, familiar environment of the activity sessions ensure the safety and well-being of participating older adults.

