**Figure 2 figure2:**
[figure not shown]
Procedure of the population-based prospective observational cohort study BeTaSen's intervention over a period of 12 months; an example is shown for 1 district (study population: older adults aged 75 years or older living in Chemnitz, Germany). BeTaSen: Bewegungs-Tandems in den Lebenswelten Chemnitzer Seniorinnen und Senioren: ein Beitrag zur kommunalen Gesundheitsförderung).

In total, around 6-8 activity tandems will be created in each of the 4 local districts (approximately 24-32 older adults per district). Thus, the goal is to reach a total of approximately 120 older adults residing in the city of Chemnitz during the project period.

Voluntary mentors (eg, volunteers from Chemnitz, students, and community center staff) will be recruited through various public channels (eg, newspapers, flyers, and mailing lists) in cooperation with municipal partners. The trained mentors should guide the activity tandem groups (eg, demonstrate PA exercises with the help of the manual and walk paths), ensure safety and well-being (eg, through individualized feedback), and encourage the older adults to do independent regular PA exercises. The mentors will also be responsible for communication and the planning of the activity tandem meetings. Researchers on the project team will instruct mentors in a workshop about how to conduct PA meetings, how to appropriately deal with the target group, and how to perform basic first aid procedures. In addition, mentors will be equipped with support materials, such as a manual that includes a range of various low-threshold PA exercises, an overview of district walkways, and additional exercise materials (eg, resistance bands and everyday objects).

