In line with previous literature and findings, the vulnerable target group’s potential barriers should be carefully considered when developing the pilot study. To ensure low-threshold accessibility, the activity tandems and monthly group meetings will take place in the older adults’ neighborhoods. District plans will be drawn up to identify sitting areas and public toilets, for example, and to pinpoint accessible walkway plans. The activity tandem’s PA content will be designed to reflect daily life activities in a very playful, individualized, ability-oriented, and motivational way. Each unit can be freely designed by the mentors and older adults based on the PA, exercise materials, and recommendations provided. Each activity tandem unit should begin with a warm-up, and the components of strength, endurance, coordination, stretching, and relaxation should be addressed regularly in different sessions. In addition, the mentor should include knowledge transfer in each unit, for example, about the positive effects of PA. Moreover, participation in the PA intervention does not entail any financial costs (eg, materials and participation fees). To promote sustainable participation in the neighborhood meetings and to ensure that the PA meetings are tailored to the vulnerable target group, the activity tandems are purposely organized for a smaller number of older adults. The older adults and mentors of the activity tandems can coordinate the time and location of their weekly meetings flexibly on their own.

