### Statistical Analysis

SPSS Statistics (version 29; IBM Corp) and AMOS (version 29; IBM Corp) will be used for all quantitative statistical analyses. To determine the primary outcome at baseline (T1), the study population will be descriptively characterized using the following outcomes: demographics (eg, age, gender, family status, and income), anthropometric comorbidities, PA and health-related behavior (eg, smoking status and alcohol consumption), as well as physical, functional, cognitive, and psychosocial health status. Furthermore, participants’ data at the end of the intervention period (T2) and 6 months after its end (T3) will be analyzed to evaluate the long-term impacts, feasibility, and usefulness of the PA intervention. Time effects, group differences (eg, age, gender, vulnerability, and sociodemographic conditions) in terms of physical, cognitive, and psychosocial health, interaction effects, as well as the intervention’s feasibility and sustainability, will be analyzed using different parametric or nonparametric statistical methods such as the *t* test, Mann-Whitney *U* test, ANOVA, or Kruskal-Wallis test, depending on the number and size of the group, normal distribution, and homoscedasticity of the sample. Based on current evidence [6-8,25], associations and the strength of the relationship between 2 variables (eg, PA behavior and monthly income and adherence rate and level of education), correlation and regression analyses as well as adjustments for relevant covariates (eg, age, gender, and vulnerable criterion) will be performed. Additionally, multilevel analyses are planned to estimate, for example, the within-person impacts of the intervention program (eg, the impact of PA on well-being).

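### Participants are treated in tandems of 3-4, but the named tests assume independent people; if outcomes correlate within tandems, standard errors for mean change and adherence will be too small

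*Protocol article*

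**What the plan says.** The section Design and Organization of a Physical Activity–Promoting Intervention in the protocol article sets out group delivery. "One activity tandem will include 1 trained voluntary mentor and 3-4 older adults living in the same neighborhood". Content is settled within the tandem: "Each unit can be freely designed by the mentors and older adults based on the PA, exercise materials, and recommendations provided". Each tandem also agrees its own meeting time and place. Above the tandem there are "monthly group meetings (eg, 3-4 activity tandems with a total of 12-16 older adults", and then districts: "around 6-8 activity tandems will be created in each of the 4 local districts (approximately 24-32 older adults per district". The recruitment aim is that "the goal is to reach a total of approximately 120 older adults residing in the city of Chemnitz". There is no comparison group: "All participants will participate in the target group-specific community-based PA intervention".

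The Statistical Analysis section offers the t test, Mann-Whitney U, ANOVA and Kruskal-Wallis as examples of methods for time effects, group differences, feasibility and sustainability. It gives a rule for choosing among them: "ANOVA, or Kruskal-Wallis test, depending on the number and size of the group, normal distribution, and homoscedasticity of the sample". Correlation and regression follow, with age, gender and the vulnerability criterion as example covariates and adherence against education as an example association. In addition, "multilevel analyses are planned to estimate, for example, the within-person impacts of the intervention program (eg, the impact of PA on well-being"; this within-person effect is the only multilevel example. Tandem, mentor and district are not mentioned in that section, and no intracluster correlation (ICC) is given.

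**The concern.** Members of one tandem share a mentor, content, schedule and location, and all of these differ between tandems. Attendance is the clearest case. The Feasibility and Usefulness section measures adherence by the number of tandem and group meetings completed, so a meeting the mentor cancels, or a tandem that stops meeting, affects every member at once. Change in activity or function may be correlated for the same reasons.

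With no control arm, the impact estimate is the pooled change from T1 to T2 and T3. That is the kind of quantity for which positive within-cluster correlation makes a naive standard error too small. The selection rule looks at group number and size, normality and equal variances, but not at dependence between participants. Followed as written, it can overstate the evidence for change and the precision of the adherence figures. It also leaves variation between mentors unseen, although that bears directly on the study's feasibility and implementation questions.

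**Working it through.** **Inputs.** Tandem size m = 3 to 4, midpoint 3.5, and N of about 120 (both from the intervention design section). The ICC is not in the article, so 0.05, 0.10 and 0.20 are assumed. No significance level is stated; two-sided 5% is used as the conventional one.

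**The plan's own figure.** The 120 comes from project period and funding, so there is no power formula to reproduce. The recruitment arithmetic is 4 × 24 = 96 to 4 × 32 = 128, which contains 120. The district totals imply tandems of four (24/6 = 4, 32/8 = 4). At that size 120 people need 120/4 = 30 tandems, inside the planned 4 × 6 = 24 to 4 × 8 = 32. At 3.5 or 3 per tandem they would need 34.3 or 40. Size 3.5 is therefore the midpoint of the stated range, and 4 fits the recruitment figures best.

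**Effect on mean change.** Design effect DE = 1 + (m − 1) × ICC. True SE / naive SE = √DE. Effective N = 120/DE. Type I error = 2 × [1 − Φ(1.96/√DE)].

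For m = 3.5 and ICC 0.10: DE = 1 + 2.5 × 0.10 = 1.25; √1.25 = 1.118; 120/1.25 = 96; 1.96/1.118 = 1.753, so the type I error is 8.0%.

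| m | ICC | DE | SE larger by | Effective N | Type I error |
|---|---|---|---|---|---|
| 3 | 0.05 | 1.10 | 4.9% | 109 | 6.2% |
| 3 | 0.10 | 1.20 | 9.5% | 100 | 7.4% |
| 3 | 0.20 | 1.40 | 18.3% | 86 | 9.8% |
| 3.5 | 0.05 | 1.125 | 6.1% | 107 | 6.5% |
| 3.5 | 0.10 | 1.25 | 11.8% | 96 | 8.0% |
| 3.5 | 0.20 | 1.50 | 22.5% | 80 | 11.0% |
| 4 | 0.05 | 1.15 | 7.2% | 104 | 6.8% |
| 4 | 0.10 | 1.30 | 14.0% | 92 | 8.6% |
| 4 | 0.20 | 1.60 | 26.5% | 75 | 12.1% |

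At ICC 0 nothing changes.

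**Check by simulation.** A one-sample test of change, 20,000 runs per setting, rejected at 6.9% / 8.4% / 11.7% for ICC 0.05 / 0.10 / 0.20 with 30 tandems of 4, and at 6.3% / 7.3% / 9.9% with 40 tandems of 3. Testing the tandem means instead gave 4.8% to 5.1%.

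**Why a tandem random intercept is not enough.** Write the outcome of person i in tandem j at time t as μₜ + uⱼ + bᵢⱼ + eᵢⱼₜ. The change from T1 to T2 is then (μ₂ − μ₁) + (eᵢⱼ₂ − eᵢⱼ₁). Both uⱼ and bᵢⱼ cancel, so the model still treats members' changes as independent. A simulation with 30 tandems of 4, two time points and complete data (400 runs per ICC) agrees. The SE of the time effect with person and tandem intercepts was 1.000 times the naive paired SE, and both analyses rejected at 8.5% for ICC 0.10 and 13.3% for ICC 0.20. Correlated change enters only through a term that lets the time effect differ by tandem, or through a tandem effect on the change score itself.

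**The case against.** The method lists are open. The tests are introduced as examples, and so is the within-person multilevel analysis, so a tandem level is neither named nor excluded. This is a condensed article, and the levels of a mixed model are often left to a fuller plan that is not shown. That stands against any claim that the plan has ruled out clustering. It does not remove the point, because the article names methods that need independence and gives a selection rule that ignores dependence.

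The ICC is assumed and could be small. Mentor contact tapers to monthly in months 7-9, with largely independent activity from month 10, while outcomes are taken at 12 and 18 months, so a mentor effect may have faded. That is a fair reason not to lean on 0.20. The tandem is still meant to go on meeting as a group, so it is no reason to assume zero.

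A reader might infer that every comparison in the section is too optimistic. The article does not support that. The comparisons it names are by age, gender, vulnerability, income and education, which can all vary within a tandem. Ignoring clustering need not narrow those intervals.

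A reader might also infer a much larger inflation from the districts, with about 30 people in each. No district ICC is given, a design effect resting on four clusters is not reliable, and district can simply be a fixed effect, in which case that design effect does not apply. No district figure is claimed here.

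Finally, this is a pilot with no stated power, significance level or confidence interval, and its Discussion acknowledges that the design is not randomized or controlled. That limitation matters more for interpretation than a modest error in the standard error. It bears on priority, not on whether the standard error is right.

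**Conclusion.** The point holds in conditional form. The named tests and regressions assume independent participants, while the design creates groups of 3-4 with shared mentor, content and schedule. If change or attendance correlates positively within tandems, standard errors for mean change, adherence and tandem- or mentor-level factors are understated. At 3.5 per tandem the true SE is about 6% to 12% larger for an ICC of 0.05 to 0.10, and about 22% larger at 0.20. Type I error is 6.5% to 8.0%, and 11.0% at 0.20. These sizes rest on assumed ICCs and a conventional 5% level.

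It would go too far to say that the intervals are certainly too narrow, since the article gives no evidence on the ICC. The correction is modest, but it should be made because the change and adherence estimates are the study's main quantitative results.

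**What to change.** In Statistical Analysis, state that change from T1 to T2 and T3 will be estimated in one of these ways:

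- with tandem-clustered standard errors, using a small-sample correction because only some 24 to 32 tandems are planned;
- with a model of change scores that has a tandem random effect;
- with a repeated-measures model that includes a tandem-by-time random effect.

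Say explicitly that a tandem random intercept alone is not relied on for the time effect. For adherence, which has one value per person, a tandem random intercept or clustered standard errors is sufficient. District can be added as a fixed effect if wanted. Report the tandem ICC for the main outcomes and for adherence; it describes variation between mentors and would inform the size of a later controlled trial.

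The cost is somewhat wider intervals. Tandem membership must also be carried in the analysis data set: the article describes individual identification codes and session documentation by tandem, but does not say that the two are linked for analysis. Where a rank-based test is kept, it cannot simply be given a random effect and would need to be run on tandem-level summaries or replaced.

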### Ethical Considerations

This study was approved by the Ethics Committee of the Chemnitz University of Technology, Faculty of Behavioral and Social Sciences, on May 19, 2022 (101547973). All study participants will be fully informed about the objectives and procedures of the study in German and will be requested to give written informed consent. Additionally, the informed consent contains information about the pseudonymized data collection for the study. Furthermore, the original informed consent allows the secondary analysis without additional consent.

## Results

The intervention period of the BeTaSen study started in August 2022 in the first neighborhoods of the City of Chemnitz. Due to the planned staggered launches of the different activity tandems, cross-section data of all participants at T1 (approximately 120 older adults) and initial feasibility data 6 months into the intervention (approximately 60 older adults) will be collected until December 2023. Longitudinal results are expected in the first quarter of 2025. Qualitative and quantitative data on sustainable components for PA interventions among all participating vulnerable older adults are expected in December 2024, after T2, and 6 months after the end of the intervention (T3).

## Discussion

The aim of the BeTaSen study is thus to develop, implement, and evaluate a target group-specific PA intervention for community-dwelling older adults living in Chemnitz, the city with the highest median age in Europe [44].

The intervention program was developed especially for the target group of vulnerable community-dwelling older adults on the basis of theoretical aspects [29-35] and considers potential barriers and facilitating factors for initiating and maintaining regular PA. Furthermore, the specific intervention design contains elements promoting long-term use (eg, increasing independent activity sessions over the intervention period, individual goal setting, and knowledge transfer of the effects of PA). Therefore, the intervention concept and their implementation are expected to contribute to (1) increasing or maintaining PA behavior, cognitive and physical function, as well as psychological parameters of older adults, and (2) the feasibility and sustainability of healthy aging in municipalities.

The results of the study will provide insights into (1) the PA behavior of vulnerable older adults as well as the impact of PA interventions on health-related outcomes such as cognitive, physical, and psychosocial health, and (2) feasible and useful components of community-based PA interventions. Thus, this pilot study bridges a research gap as it focuses on the PA-promotion of vulnerable community-dwelling older adults and implements a low-threshold health promotion concept that may have a sustained impact on the health and health-related behavior of this specific target group. Furthermore, the BeTaSen study will make an important contribution to the state of knowledge of average PA levels and health outcomes, as well as the impact, feasibility, and sustainability of such interventions. As the results of the study will provide insight into the demands, needs, and possible barriers of programs, it can provide a foundation for new interventions and how to deal with difficulties in their implementation.

During and at the end of the project period, interim results and findings will be summarized in information brochures and presented at municipal information events or scientific congresses. When interpreting the results, it should be considered that this research project does not have a randomized, controlled study design since the accessibility of the target group is very restricted and community-based PA programs should be accessible to vulnerable older adults over the entire study period. Nonetheless, the results of the study will provide insights into the within-person impacts of regular PA over a longer time period, and the study design comprises a low-threshold intervention for a highly relevant target population and allows “real-world” applicability. The results of the study will make an important contribution to the research field of aging and movement sciences as well as to the development of health-promoting structures, providing insights into the impact and implementation strategies of community health promotion programs for specific target groups like vulnerable older adults. In addition to publications in scientific journals, the impulses of the study will be implemented into municipal health policies and structures (eg, other neighborhoods, community centers, and health departments) after the end of the project period. Furthermore, the PA program can be distributed throughout Germany through cooperation with the Federal Centre for Health Education and thus shows a high potential for expansion.

Finally, the results will contribute to future recommendations and provide a basis for further research, such as the development of feasible and sustainable target group-specific interventions in community settings.

## Abbreviations

BeTaSen: Bewegungs-Tandems in den Lebenswelten Chemnitzer Seniorinnen und Senioren: ein Beitrag zur kommunalen Gesundheitsförderung
MoCA: Montreal Cognitive Assessment
PA: physical activity
PRISCUS-PAQ: PRISCUS-Physical Activity Questionnaire
SPPB: Short Physical Performance Battery
TMST: 2-minute step test
WHO: World Health Organization
